#### Exclusion Criteria

Patients under the age of 18 will be excluded.

Patients assessed to be comorbid (eg, life expectancy less than 6 months) were not deemed to be suitable candidates for temporary mechanical support or long-term, durable mechanical circulatory support and were excluded in principle from data abstraction

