**Objective:**

The objectives of this study are (1) to collect retrospective clinical outcomes for acute decompensated heart failure cardiogenic shock and acute myocardial infarction cardiogenic shock, and compare current versus historical survival rates and clinical outcomes; (2) to evaluate Inova Heart and Vascular Institute site specific outcomes before and after initiation of the Cardiogenic Shock team on January 1, 2017; (3) to compare outcomes related to early implementation of mechanical circulatory support and hemodynamic-guided management versus historical controls; (4) to assess survival to discharge rate in patients receiving intervention from the designated shock team and (5) create a clinical archive of Cardiogenic Shock patient characteristics for future analysis and the support of translational research studies.

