**Methods:**

This is an observational, retrospective, single center study. Retrospective and prospective data will be collected in patients treated at the Inova Heart and Vascular Institute with documented cardiogenic shock as a result of acute decompensated heart failure or acute myocardial infarction. This registry will include data from patients prior to and after the initiation of the multidisciplinary Cardiogenic Shock team on January 1, 2017. Clinical outcomes associated with early multidisciplinary team intervention will be analyzed. In the study group, all patients evaluated for documented cardiogenic shock (acute decompensated heart failure cardiogenic shock, acute myocardial infarction cardiogenic shock) treated at the Inova Heart and Vascular Institute by the Cardiogenic Shock team will be included. An additional historical Inova Heart and Vascular Institute control group will be analyzed as a comparator. Means with standard deviations will be reported for outcomes. For categorical variables, frequencies and percentages will be presented. For continuous variables, the number of subjects, mean, standard deviation, minimum, 25th percentile, median, 75th percentile and maximum will be reported. Reported differences will include standard errors and 95% CI.

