A designated, multidisciplinary shock team is critical in the assessment, implementation, and management of the CS patient. The collaborative efforts of a team which includes a cardiologist specializing in heart failure, a cardiothoracic surgeon, cardiac inteventionalist, and an intensive care unit (ICU) intensivist working to manage the time-dependent clinical scenario will maximize outcomes related to CS [5]. The Cardiogenic Shock team at the Inova Heart and Vascular Institute (IHVI) is comprised of four clinical disciplines: Interventional Cardiology, Acute Heart Failure, Cardiac Surgery, and Critical Care. Their respective roles in the diagnosis, treatment and management of cardiogenic shock are highly specific yet profoundly collaborative. Interventional cardiology is at the vanguard of treatment and is usually the first point of contact. This group assists with mechanical circulatory assist device insertion and management both on hospital admission and throughout hospitalization. They also manage device weaning and escalation of support. The acute heart failure physician specialist helps to determine a patient’s candidacy for temporary and durable mechanical support. The role of the cardiac surgeon is to assist with and evaluate a patient’s candidacy for surgical support services. Finally, the critical care physician is the team quarterback and the central player in identifying the appropriate parties for emergency consultation as well as the advancement and management of the cardiogenic shock patient’s day-to-day care during hospitalization. IHVI CS team goals can be identified as follows: rapid identification of CS as well as its etiology, maximization of survival through the utilization of mechanical circulatory support (intraortic balloon pump; Impella, percutaneous microaxial flow pump; Tandem Heart, percutaneous left ventricular assist device; peripheral extracorporeal membrane oxygenation [ECMO]; central ECMO; temporary vascular assist device; permanent vascular assist device; or transplant) as well as supportive therapies, and the development and implementation of a hemodynamic support plan with mechanical devices in the event of refractory CS [5]. Team-based interventions are crucial in critical illness as in the case of a “code team” (mandated by the Joint Commission on Accreditation of Healthcare Organizations) for the in-house management of cardiac arrest and a rapid response team for decompensating medical surgical patients. CS is similar to these clinical clusters of symptoms and requires the early identification and specific expertise of many disciplines in order to manage this complex condition. The high mortality rate of CS patients can be tempered through early revascularization and the activation and utilization of a multidisciplinary shock team. The time sensitive nature of CS or the dictum “time to support” [6], with both percutaneous and surgical interventions, requires the activation of a multidisciplinary Shock team in order to manage circulatory collapse and the ensuing end organ dysfunction [6] or failure through prompt response and management of any changes in the patient’s condition in addition to early diagnosis.

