#### Inclusion Criteria

Patients at the IHVI with documented Cardiogenic Shock team intervention for acute decompensated heart failure cardiogenic shock, or acute myocardial infarction cardiogenic shock.

Specific criteria for the diagnosis of cardiogenic shock is defined by hemodynamic parameters—systolic blood pressure <90 mm Hg, cardiac index <1.8 L/min/m^2^ without pharmacologic support (or >2.2 L/min/m^2^ with support), left ventricular end-diastolic pressure >18 mm Hg or right ventricular end-diastolic pressure >10-15 mm Hg or pulmonary capillary wedge pressure >15 mm Hg—and clinical signs and symptoms of hypoperfusion, such as cool extremities, decreased urine output, and altered mental status.

Enrollment criteria are specific to patients treated at the IHVI for documented cardiogenic shock with activation of the IHVI Cardiogenic Shock team. Cardiogenic shock will have preceded acute decompensated heart failure or acute myocardial infarction etiologies. Patients will include those transferred from offsite hospitals as well as inpatients at the IHVI.

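### The poor-prognosis exclusion is discretionary and not tied to both eras, so the protocol does not ensure that it acts equally on the team and historical groups

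*Protocol article*

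**What the plan says.** The Exclusion Criteria state that patients assessed as comorbid, with a life expectancy under six months as the example, "were not deemed to be suitable candidates for temporary mechanical support or long-term, durable mechanical circulatory support and were excluded in principle". The exclusion takes effect when data are abstracted. Apart from the six-month example the rule gives no threshold, and it names no assessor, time point or group.

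On who judges candidacy, Background and Significance says: "The acute heart failure physician specialist helps to determine a patient’s candidacy for temporary and durable mechanical support". That specialist belongs to the Shock team, and the same section gives candidacy for surgical support to the team's cardiac surgeon. The Objective dates the team's start to January 1, 2017.

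On who is eligible, the Inclusion Criteria say: "Enrollment criteria are specific to patients treated at the IHVI for documented cardiogenic shock with activation of the IHVI Cardiogenic Shock team". Age of Subjects likewise refers to patients who had team intervention. The Abstract (Methods) adds: "An additional historical Inova Heart and Vascular Institute control group will be analyzed as a comparator". No eligibility rule for that group is given. The same paragraph includes every patient with documented shock whom the team evaluated and treated. Participant Eligibility Criteria, under Research Database Participation Eligibility, takes in any patient treated for cardiogenic shock at the institute. Neither mentions comorbidity or candidacy for support.

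Primary Outcomes names all-cause mortality at hospital discharge and the comparison of current with historical survival.

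**The concern.** An exclusion based on expected death acts directly on a mortality outcome. It does little harm to a before-and-after comparison if it removes the same kind of patient, in the same proportion, from both periods. Nothing in the article secures that.

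- The trigger is a judgement, illustrated by one example and applied only in principle.
- It is linked to candidacy for mechanical support, and the article makes the assessment of candidacy part of what the team does. The 2015–2016 patients had no such team, so for them the judgement would have to come from other chart evidence.
- The written inclusion rules cannot be met by a pre-2017 patient, so a reader cannot tell which exclusions apply to the controls.
- The exclusion acts at abstraction. Patients dropped there never enter the research database, and no later analysis can recover them without returning to the charts.

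If the rule is used more heavily in the team era, the survival estimate for that era rises without any effect of the team. That is the direction the Hypothesis predicts.

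**Working it through.** **Inputs from the article.** Results gives 2017 survival as 57.9% (81/140) and baseline 2016 survival as 47.0%. The first reproduces: 81/140 = 0.579. The gain is 57.9 − 47.0 = 10.9 points. I treat the two rates as the same measure of survival.

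**Inputs assumed.** The article gives neither the share of patients excluded, f, nor their survival, s. I take f = 10–20% and s = 0–10%.

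**Step 1: all-comer survival.** If a share f of all patients was left out, all-comer survival = (1 − f) × reported survival + f × s. For 2017 with f = 10% and s = 10%: 0.90 × 57.9 + 0.10 × 10 = 53.1%. With f = 20% and s = 0: 0.80 × 57.9 = 46.3%.

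**Step 2: three ways of treating the controls.** The same formula is applied to the 47.0% with a control share of 0, f/2 or f, and the same s.

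| f (team era) | s | 2017 all-comer survival | Gain, controls not excluded | Gain, controls at f/2 | Gain, controls at f |
|---|---|---|---|---|---|
| 10% | 10% | 53.1% | 6.1 | 8.0 | 9.8 |
| 10% | 0% | 52.1% | 5.1 | 7.5 | 9.8 |
| 20% | 10% | 48.3% | 1.3 | 5.0 | 8.7 |
| 20% | 0% | 46.3% | −0.7 | 4.0 | 8.7 |

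The last column is (1 − f) × 10.9 and does not depend on s.

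**Step 3: break-even with exclusion in the team era only.** Setting all-comer survival to 47.0% gives f = (57.9 − 47.0)/(57.9 − s). For s = 0, f = 10.9/57.9 = 19%. For s = 10%, f = 10.9/47.9 = 23%.

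**Step 4: the planned comparison with no true effect.** Let true survival be 47% in both eras, with 200 patients per group before exclusion. Apparent team-era survival is (0.47 − f × s)/(1 − f). Excluding 20% of the team era only gives (0.47 − 0.04)/0.80 = 53.8% for s = 20%, and 0.47/0.80 = 58.8% for s = 0. These are spurious gains of 6.8 and 11.8 points. At a two-sided level of 0.05 (assumed; the article prints 0.5), a significant gain would appear in about 25% and 60% of studies. With controls excluded at half that share, 3.8 to 6.5 points remain. With equal f and s in both eras, the spurious gain is 0.

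**The case against.** The strongest reply is that the article never says the exclusion was confined to the team era. It stands under the general Exclusion Criteria and names no group. Its stated trigger is comorbidity or short life expectancy, with unsuitability for support as the consequence, and a terminal illness could be found in a chart from either era. A reader might infer that expected deaths were removed from the team group and left among the controls, or that nobody assessed candidacy in 2015–2016. The documents support neither. They also do not say whether the 47% was calculated before or after the same exclusion. This part of the reply stands, and for that reason the equal-exclusion column belongs beside the one-sided one.

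A reader might also infer that this mechanism explains the preliminary results. It could match the 2017 gain only under one-sided exclusion of about a fifth of patients. The 2018 figure of 81.3% (26/32) would need 42–56% excluded (s = 0–20%), which is unlikely.

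Nor do I press a claim that the rule damages the comparison of support with no support in Specific Aims. Leaving out patients who could not have received support can reduce confounding by indication there.

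Two further replies carry less weight. Study Type acknowledges possible selection bias against historical controls, but only in general terms and as a result of the changed treatment paradigm; it neither mentions nor limits this exclusion. An article may leave abstraction detail to the full protocol. Here, however, it states an eligibility rule, and that rule conflicts with two of its own descriptions of who is included.

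**Conclusion.** The point holds as a failure to ensure equal application; bias has not been shown. The article sets a prognostic, discretionary exclusion linked to a judgement assigned to the new team. It gives the controls no eligibility rule and elsewhere admits patients without this restriction. Following it as written permits bias towards the hypothesis on a primary outcome.

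The size depends on shares the article does not give. With 10–20% of 2017 patients excluded at 0–10% survival, the 10.9-point gain becomes between −0.7 and 6.1 points if only the team era is affected. It becomes 8.7 to 9.8 points if both eras are affected alike. The article offers no means of telling where between these the study lies. This is more than a missing detail, because the exclusion acts before the data exist.

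**What to change.** 1. Abstract all adults meeting the article's haemodynamic definition of cardiogenic shock in both eras, whatever their comorbidity or candidacy for support, and use them for the primary comparison of current with historical survival.
2. Replace the present exclusion wording with one objective criterion documented before the shock episode. Apply it identically in both eras and without reference to outcome, as a sensitivity analysis only.
3. Report, by era, how many patients meet that criterion and their survival.
4. Reconcile the Abstract (Methods), Inclusion Criteria, Exclusion Criteria and Participant Eligibility Criteria, and state the eligibility rule for the historical controls.

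The cost is some additional chart abstraction, including a return to 2017 charts already reviewed, and possibly a lower team-era survival estimate. The change concerns only who is counted in the analysis, not how patients are treated.

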### Research Database Participation Eligibility

#### Participant Eligibility Criteria

Any patient with cardiogenic shock, whether inpatient or transferred from another facility, treated at the Inova Heart and Vascular Institute. This includes adults with and without decision making capacity over the age of 18 years old.

#### Informed Consent

Informed consent is waived for the purpose of this research database. The procedural risk involved in this protocol meets the definition of minimal risk as set forth in 45 CFR 46.102 (i) “Minimal risk means that the probability and magnitude of harm or discomfort in the research are not greater in and of themselves than those ordinarily encountered in daily life or during the performance of routine physical or psychological examinations or tests.” Participation in this protocol requires evaluation of medical data from patients who have experienced CS that is mined directly from the participant’s medical record.

#### Registry Data

The primary investigator will designate the data points to be included in the database in order to assess the efficiency of procedures and protocols in the treatment of CS at the IHVI as administered by the Shock team, to identify relationships between treatment and negative morbidity and mortality outcomes, and to monitor and improve quality of care delivered.

In addition to the defined data collected, additional participant data may be collected as needed for a specific study. This additional data would be contained in the participant’s medical records. Examples of this additional data that may be requested for a related additional study would be more detailed clinical data at the time of diagnosis or more detailed disease status data while experiencing cardiogenic shock. In no case will the participant be contacted in order to obtain additional data.

#### Collaboration With Other Registries

To facilitate both national and international research efforts in cardiogenic shock patient’s collaborative studies may occur with other institutions outside of Inova. Detailed patient-level data obtained through the cardiogenic shock database can facilitate hypothesis-driven clinical studies. The information in the database will not only be utilized to drive internal investigator-driven projects but also be used to foster collaborative studies with institutions outside of INOVA. For any collaborative studies with outside institutions, a data use agreement will be in place. Dataset exporting will be restricted to the database manager and the primary investigator. Only a limited data set will be provided which includes dates to help identify clinical events. No other protected health information will be such as name, contact information, medical record identification number nor any other patient- specific identifiers will be provided to these collaborative partners. In addition, collaborative studies using the cardiogenic shock database will not be approved unless authorized by the principal investigator alone and the aforementioned data use agreement has been executed.

#### Data Confidentiality

Access to all information in the Cardiogenic Shock Research Database is securely controlled utilizing passwords and logins at multiple levels. Access to the research data base is limited to relevant IRB approved study team members and to employees with specific job responsibilities related to the database.

Registry participants are assigned a unique identification (UID) number when they are enrolled into the cardiogenic shock database. All protected health information (PHI) will be fully de-identified. The UID contains no identifying information. This UID is utilized to track all participant information in the research database. Protected health information is defined as:

NameGeographical subdivisions smaller than StateTelephone numberFax numberElectronic mail addressesSocial security numbersMedical record numbersHealth plan beneficiary numbersAccount numbersCity, state, and country

Or any other specific identifying information will be collected at the time the unique identification number is assigned to ensure that the participant has not been previously registered. Identifying data will be stored in a secure database separate from the research database. This protected information will not be included in data sets used for analysis. The unique identification number will have no identifying information within it. This number will be used to track all information about the participant in the research database.

The identity of the database participants will be kept confidential at all times. All research staff at INOVA will maintain up-to-date training in protection of human subjects. This training is received through the Collaborative IRB Training Initiative program. This is a Web-based training program offered through the University of Miami.

### Endpoints or Outcome Measurements

#### Primary Outcomes

The primary outcomes of this study are to create an archive of retrospective clinical outcomes (acute decompensated heart failure cardiogenic shock, or acute myocardial infarction cardiogenic shock) and compare current versus historical survival rates and to evaluate all-cause mortality at hospital discharge.

#### Secondary Outcomes

Analysis of mortality by subgroup (age, sex, initial etiology, time to presentation, time to treatment, use of mechanical circulatory support, Incidence of major adverse cardiac and cerebrovascular events, and preservation of left ventricular function.

### Statistical Considerations and Data Analysis

#### Sample Size

We are estimating 300-400 patients will be included in this analysis. This size is based on prior smaller studies.

#### Method of Data Analysis

Data will be collected from a chart review and recorded in a database spreadsheet. Statistical analysis will be performed to calculate data collected in this study. Results will be reported using summary tables and will be displayed for each treatment arm. For categorical variables, frequencies and percentages will be presented. For continuous variables, the number of subjects, mean, standard deviation, minimum, 25th percentile, median, 75th percentile and maximum will be presented. Reported differences will include standard errors and 95% CI.

#### Data Storage

##### Data Management

Designated study site staff will directly query EPIC and retrieve a set of defined data fields that can be directly integrated into INOVA’s clinical or translational research database, REDCap. Specific forms will be used for each component of the subject’s progress. The forms and data dictionary will be available online for all individuals who perform data entry. Research personnel, trained on data definitions will perform logical data checks to assess data quality. Suspect data entries will be flagged for review and confirmed by the investigative team at each site.

Information about study subjects will be kept confidential and managed according to the requirements of the Health Insurance Portability and Accountability Act of 1996. Privacy and confidentiality of all patients enrolled will be maintained. Steps will be taken to “de-identify” participants from their personal health information (PHI) by assigning each patient a PIN number that will not be linked to any specific PHI. The “key” linking the PIN to the patient’s PHI will be maintained separately from the collected data and will be stored on a protected data file on a secure internet server requiring password login.

##### Records Retention

The investigator will maintain records in accordance with ICH Guidelines. Essential records will be stored for no longer than 3 years after the study is formally discontinued and then destroyed. Paper records will be shredded and recycled. Records stored on a computer hard drive will be erased using a commercial software application designed to remove all data from the storage device.

### Human Subjects Protection (Risks, Benefits, and Alternatives)

#### Risks

There are no anticipated significant risks in this study. Potential loss of confidentiality will be minimized by shielding the participants by unlinking his or her identity from his or her personal health information

#### Benefits

There are no direct benefits to the patient.

#### Confidentiality

The Principal Investigator and Coinvestigators will be ultimately responsible for assuring the security of all computer systems to minimize risk to participants. The participant’s identifiable private information will be handled, managed, and disseminated in a method which places confidentiality as the highest priority. Individuals who will have access to the data will need to be clearly delineated. The data will be stored in a Health Insurance Portability and Accountability Act of 1996 (HIPPA) compliant database, shared only with individuals who are participating in the study, and will be stored for no longer than 3 years and then eventually destroyed.

